### Dyadic Characteristics: Analysis of the Scale Data Over Time

Repeated-measures analyses using mixed linear models will be performed for scale data. These analyses will include participant-level characteristics and couple-level variation or clustering. Participants will be nested within couples with the participant as the experimental unit. Repeated-measures analyses for each scale will be analyzed with a means model with SAS Proc Mixed providing separate estimates of the means by time on study and treatment group. An unstructured variance-covariance form among the repeated measurements will be assumed for each outcome, and estimates of the standard errors of parameters will be used to perform statistical tests and construct 95% confidence intervals. T-tests will be used to compare the pairwise differences between the model-based treatment means (least-squares means) at each time point. Statistical tests will be 2-sided. The model-based means are unbiased with unbalanced and missing data if missing data are noninformative (missing at random). A dropout process is assumed to be missing at random if, conditional on the observed data, the dropout is independent of the unobserved measurements.

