## Methods

### Design

The research activities involve a prospective RCT of approximately 165 venue- and clinic-recruited sero-discordant male couples (330 individuals: 165 HIV sero-negative and 165 HIV sero-positive). The study takes place in three cities: Atlanta, GA (study site Emory University); Boston, MA (study site The Fenway Institute); and Chicago, IL (study site Ann & Robert H. Lurie Children’s Hospital of Chicago). Cohort recruitment began in 2015. Couples are followed prospectively for 24 months, with study assessments at baseline, 6, 12, 18, and 24 months.

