#### Dyadic Characteristics

The four elements of Lewis’ model [57] (*predisposing factors of couples*, *partner’s transformation of motivation*, *process of communal coping*, and *use of communal coping*) are referred to as *dyadic characteristics*. In a recent RCT of CHTC, scales were developed to capture these constructs; all scales showed strong reliability, and evidence for construct validity was obtained for all scales [60]. In this intervention, each of the scales is collected in the baseline and follow-up surveys.

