#### Predisposing Factors

Predisposing factors of couples uses several scales to measure this element. *Perceived Severity of HIV Scale:* this construct involves the perception of the personal, psychosocial, and physical consequences of a particular health threat. A total of 13 items were developed that crossed the three pertinent consequences of a particular health threat: personal, psychosocial, and physical. *Preferences for General Lifestyle Outcomes Scale*: this construct is defined as the degree to which interacting partners agree about the shared or joint outcomes in their relationship, which is composed of two subscales (*Preferences for General Lifestyle Scale* and *Preferences for Sexual Health Outcomes Scale*). The *Preferences for General Lifestyle Scale* includes six outcomes, including diet, nutrition, and social activities. *Preferences for Sexual Health Outcomes Scale* relates to sexual health (eg, reducing one’s risk for HIV). In addition, scales to measure other predisposing factors of couples are proposed for inclusion. *Conflict Style* determines how respondents typically handle conflict in their relationships, so the Conflict Style Inventory will be included [61]. *Communication Style* is measured with the Communication Patterns Questionnaire Constructive Communication subscale [62]. Finally, *Problem-Solving Skills* are measured with the adherence problem solving/readiness scale [63].

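### The arm contrasts on the dyadic scales are, as written, not adjusted for the baseline score that is collected, so they are valid but less precise than the data allow; no single contrast per scale is designated

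*Protocol article*

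**What the plan says.** The section on the analysis of the scale data over time specifies a mixed linear model for each scale, "providing separate estimates of the means by time on study and treatment group", with an unstructured covariance over the repeated measurements. On covariates and clustering it says: "These analyses will include participant-level characteristics and couple-level variation or clustering". The comparison is then fixed: "T-tests will be used to compare the pairwise differences between the model-based treatment means (least-squares means) at each time point". It adds: "Statistical tests will be 2-sided". Intervals are at 95%, which implies 5% per comparison.

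The Design section sets the visits, "with study assessments at baseline, 6, 12, 18, and 24 months". The Dyadic Characteristics section says that "each of the scales is collected in the baseline and follow-up surveys".

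The article does not name the baseline score as a covariate of the scale models, does not set the baseline means equal across arms, and does not define the effect as a change from baseline. By contrast, the section on at-risk sex does list its baseline covariates (race, age and duration of relationship). No summary contrast or main time point is designated for any scale.

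**The concern.** In a randomised trial any difference between arms in the pre-randomisation score is due to chance. A model that gives each arm its own baseline mean uses no knowledge of that fact, so with complete data the month-24 contrast is simply the arm difference at month 24. A participant's own baseline score usually predicts his later scores, and here it is already in hand. Not using it to adjust the contrast widens the intervals for nothing.

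The second part is the number of contrasts. Arms are compared at every time point on every scale and nothing says which comparison answers the question for a scale. If the intervention changed none of the scales, a few visit-specific results would still be expected to cross 5%.

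The Introduction places partnership characteristics on the possible causal pathway, and the Sample Size section claims power for the dyadic constructs. Both precision and clarity about the main contrast therefore have some value, although these are not the primary outcomes.

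**Working it through.** **The plan's own figure.** The Sample Size section gives 75 couples per group for a two-sided two-sample t-test on the dyadic constructs. It states no difference, SD, correlation or power level for them, so the figure cannot be reproduced. It can only be turned round: 75 per group at two-sided 5% and an assumed 80% power detects (1.960 + 0.842) × √(2/75) = 0.457 SD by the normal formula, or 0.460 SD by the t-test. I use 0.46 SD below as an assumed difference.

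**What the free-means contrast is.** Take 75 per arm, one observation per couple, SD 1, five visits and an assumed common correlation of 0.6.
- Complete data, baseline means free: SE at month 24 = √(2/75) = 0.163, the same as the unadjusted arm difference.
- Complete data, common baseline mean: SE = √(2 × (1 − 0.6²)/75) = 0.131.
- In a simulation of 400 runs the free-means estimate and the plain arm difference agreed to rounding error (SE 0.169 for both, against 0.140 with a common baseline mean).
- With about 20% dropout, the simulated SEs were 0.188 (plain difference), 0.178 (free-means model) and 0.145 (common baseline mean). The repeated-measures model recovers some information when data are missing, but most of the gain still comes from the baseline constraint.

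**Gain in variance and power.** Adjustment multiplies the variance by 1 − ρ², which is the same as dividing the standardised difference by √(1 − ρ²). The planned 80% retention gives 165 × 0.80 = 132 couples, or 66 per arm. Early retention in the Results section (160 enrolled, above 90% at 24 months) would give about 160 × 0.90/2 = 72 per arm. Power for 0.46 SD by the two-sample t-test:

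| ρ (assumed) | Variance removed | Power, 66 per arm | Power, 72 per arm |
|---|---|---|---|
| no adjustment | 0% | 75% | 78% |
| 0.3 | 9% | 79% | 82% |
| 0.5 | 25% | 86% | 89% |
| 0.6 | 36% | 91% | 93% |

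**Number of contrasts.** Counting from the scale descriptions:
- Predisposing factors: 6 (perceived severity; the preferences scale, "which is composed of two subscales"; conflict style; communication style; problem-solving).
- Transformation of motivation: 2.
- Communal coping: 4 (three outcome-efficacy subscales and couple efficacy).

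That is 6 + 2 + 4 = 12, and 12 × 4 follow-ups = 48. The count is 10 × 4 = 40 if outcome efficacy is scored as one total, and 12 × 5 = 60 if the baseline visit counts as a time point. At 5% each, with no true difference, the expected number of false positives is 48 × 0.05 = 2.4 (2.0 to 3.0 over that range), whatever the correlation.

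The chance of at least one is 1 − 0.95^48 = 91% if the tests were independent, which they are not. With assumed correlations of 0.3 to 0.7 between scales and 0.6 to 0.7 between visits, simulation puts it between about 50% and 79%.

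One contrast per scale would leave 12 tests and 12 × 0.05 = 0.6 expected false positives.

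**The case against.** The best defence is that nothing here is incorrect. A free-means repeated-measures model with visit-wise contrasts of least-squares means is a standard analysis, and chance baseline imbalance does not bias it. That stands, and the point is one of precision.

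A reader might infer that the scales are compared by raw t-tests and that baseline goes unused. The text does not support that. The tests are on model-based means from a mixed model with couple clustering and participant-level characteristics. Baseline is one of the repeated visits, so it plausibly sits in the outcome vector, where it helps under dropout. Nor do participant-level characteristics exclude a baseline score; it is just not named.

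A reader might also infer that spurious findings are nearly certain and would distort the account of mechanism. Near-certainty needs independent tests, and related scales measured repeatedly on the same men are not independent. No section selects mediators by visit-wise p-values: mediation has its own procedure and depends on a significant effect on the primary outcomes. The scales are additional outcomes, and multiplicity rules for such outcomes are commonly left to an analysis plan that is not shown. So the test count supports designating one contrast per scale, but it is not a defect that stands alone.

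Finally, the power figures rest on an assumed difference and one observation per couple, whereas the article makes the participant the experimental unit and surveys both partners. They show the direction and rough size of the gain and are not a forecast of this trial's power.

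What survives is that the article does more than leave a detail open. It states the mean structure, the covariance and the contrast, and that stated combination does not adjust for baseline.

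**Conclusion.** The point holds as a matter of efficiency. As specified, and apart from missing data, the follow-up contrasts on the dyadic scales are not adjusted for a baseline score that is collected for every scale. The contrasts are unbiased but less precise than they could be, by about ρ² of the variance. The gain is small at ρ = 0.3 (about 4 percentage points of power at 66 per arm) and worthwhile at 0.5 to 0.6 (about 11 to 16 points). The documents do not give ρ, and the power figures also depend on the assumed 0.46 SD and one observation per couple.

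The roughly 48 visit-wise tests (40 to 60 by counting rule) are a subsidiary reason to designate one contrast per scale. The primary outcomes are not affected.

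**What to change.** In the scale models, keep baseline in the repeated-measures vector but constrain its mean to be equal in both arms, or take baseline out of the vector and enter it as a covariate. Do not test the baseline difference. Preferably name one contrast per scale as its test, for example the arm difference averaged over the four follow-ups, and report visit-specific differences with 95% intervals as description. Label the scale results exploratory, because 12 tests remain.

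No new data are needed. The cost is a change to the model and contrast statements, and visit-specific p-values are no longer the main result. An averaged contrast can also dilute an effect confined to one visit, which the visit-specific intervals would still show.

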### Incidence of Aggregate “Sex at Risk” Within Partnerships

At-risk sex will be defined as any CAI that occurs within the partnership during the follow-up period, even if the HIV-negative partner is taking PrEP or the HIV-positive partner has achieved viral suppression, in accordance with current CDC recommendations on PrEP and condom use [65]. The incidence of at-risk sex acts will be calculated as an incidence density, with the numerator being number of individual at-risk sex acts, and the denominator being person-years of follow time. Comparisons of the incidence of at-risk sex acts will be made by comparing incidence densities between the two arms. Incidence rates per couple-year of follow-up will be estimated and compared using exact methods based on the Poisson distribution when there are fewer than 15 events per subgroup or, when there are at least 15 events per group, by using the GEE approach. Baseline covariates include race, age, and duration of relationship. Period incidence rates (6-monthly incidence density rates) of at-risk sex will be estimated by performing a GEE Poisson regression analysis of the 6-monthly counts, implemented using the SAS PROC GENMOD procedure [66], and using an exchangeable correlation structure for the repeated observations of couples. The incidence density ratio (or incidence rate ratio; IRR) is the ratio of the incidence density in one treatment group (intervention arm) to that of a control group (standard of care). Results by each baseline covariate will be summarized as the IRR and the 95% confidence interval. In addition, we will tabulate data on disclosure of sex outside the relationship, the percentage of couples with agreements about sex outside the relationship, and the percentage of couples reporting agreement breakage or change in agreements. Prevalence of each outcome will be calculated, and prevalence of outcomes will be compared in the control and intervention groups using Chi-square tests or Fischer’s exact tests, as appropriate.

The analysis will also examine conceptual mediators and epidemiologically identified moderators. If the Stronger Together intervention works to increase viral suppression and number of participants reporting full engagement in care among the intervention sample in significantly greater magnitude than the comparison condition, we will assess the extent to which this relationship works through several possible mediators, including dyadic factors and relationship functioning (ie, communication). For mediation analyses, we will employ MEDIATE procedures. MEDIATE estimates the total, direct, and indirect effects of causal variable(s) on the outcome variable through a proposed mediator variable or set of mediator variables. For effect modification (moderation) analyses, we will add interaction terms one-by-one for the intervention condition and the potential moderators (eg, age, race/ethnicity, and psychosocial factors such as depression and length of relationship). Significant or large interaction terms would suggest that the effects of the intervention differ for different subgroups, as defined by the moderators.

The analysis will also examine HIV sero-conversion among HIV-negative partners and syphilis as secondary outcomes: the prevalence and 24-month cumulative incidence of HIV and syphilis will be examined in aggregate and then by study arm. During the interim assessment visits (that occur before month 12 and then again before month 24) we will collect information on STI testing/diagnosis/treatment that participants received elsewhere since their last study assessment visit. These data will be used to adjust analyses. Using Cox proportional hazard regression models, we will assess if intervention status results in decreased odds (hazard ratio) of HIV and STI infection, separately, over the 24-month period.

The safety of the intervention at the individual level will be assessed by examining reported IPV within the relationship and relationship dissolution. Prevalence of each individual adverse outcome or any adverse outcome will be calculated, and prevalence of outcomes will be compared in the control and intervention groups using Chi-square tests or Fischer’s exact tests, as appropriate.

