### Couple Dissolution

If a couple does not remain together throughout the follow-up period, HIV-positive partners will be retained in the study for the full 2-year follow-up period, while HIV-negative partners will return for one more follow-up visit and then will be censored from the cohort. If an HIV-positive partner in the intervention arm obtains a new partner who is eligible for the study, that partner will be invited to attend further follow-up visits, to continue providing CHTC to the original positive partner with the new partner. This new partner will participate in surveys, sample collections, counseling sessions and bi-monthly phone calls. At the Boston site, new negative partners are also invited to enroll if they are in the control arm.

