As secondary outcomes, the study measures sexual risk-taking and formation, and adherence of sexual agreements. For sexual agreements, participants are asked which of the following best describes their current sexual agreement with their main partner: (1) *both of us cannot have sex with outside partners*, (2) *we can have sex with outside partners, without any conditions or restrictions*, (3) *we can have sex with outside partners, but with some conditions or restrictions*, and (4) *we do not have an agreement*. Comparison of individual data will allow identification of discordant agreements. Participants will be asked if they have broken this agreement and whether this breakage was disclosed to their partner. To assess sexual behavior, measures adapted from the National HIV Behavioral Surveillance (NHBS) behavioral inventory collect information both on sexual behaviors with the main sex partner in the 3 months before the interview, and on sexual behaviors with all sex partners outside the relationship. For sex with the main partner, men are asked to estimate the number of anal sex acts with the main partner and the number of those acts that were condom-protected. For each partner outside the relationship, men are asked a series of questions to include characteristics of the outside partner, HIV status (if known), whether the sex outside the relationship was disclosed to the main partner, the number and type of sex acts, and the proportion of those sex acts that were protected by condoms. Additional outcomes assessed are centered on Couple’s Interdependence Theory.

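### The at-risk sex rate sets acts recalled for 3 months against 6-monthly follow-up time and names two denominators, so absolute rates are understated about twofold unless rescaled; the between-arm ratio is largely protected

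*Protocol article*

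**What the plan says.** All references are to the Protocol article.

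- **Incidence of Aggregate 'Sex at Risk' Within Partnerships:** the event is any condomless anal intercourse within the partnership during follow-up. The incidence density is formed "with the numerator being number of individual at-risk sex acts, and the denominator being person-years of follow time". Shortly afterwards the unit changes: "Incidence rates per couple-year of follow-up will be estimated". Period rates come from "performing a GEE Poisson regression analysis of the 6-monthly counts", with an exchangeable correlation for repeated observations of couples. Arms are compared by the incidence rate ratio (IRR), intervention over control.
- **Outcomes:** the survey covers "sexual behaviors with the main sex partner in the 3 months before the interview". On the count itself: "men are asked to estimate the number of anal sex acts with the main partner and the number of those acts that were condom-protected". The questions go to the men individually, so each act can be reported twice.
- **Design:** "Couples are followed prospectively for 24 months, with study assessments at baseline, 6, 12, 18, and 24 months".
- **Couple Dissolution:** after a break-up, "HIV-positive partners will be retained in the study for the full 2-year follow-up period", while the HIV-negative partner attends one more follow-up visit and is then censored.
- **Follow-Up Visits:** the bi-monthly calls are described as covering the relationship and medication adherence; sexual behavior is not listed.

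**The concern.** A rate needs a numerator and a denominator that refer to the same time. Here the acts come from a 3-month window before each visit, while the stated denominator is follow-up time and the modelled counts are described as 6-monthly. The article names no source for the other 3 months of each interval and no rescaling. Read as written, half the observation time contributes to the denominator but cannot contribute acts.

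The unit is also unsettled. One couple-year is two person-years when both men are followed, and both men report the same acts. Without a counting rule, the same data can give rates that differ fourfold.

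Person-time also continues after a separation, when no further act within the original partnership can be counted. At stake are the published incidence densities for a named secondary outcome and, to a smaller degree, the rate ratio if separations differ by arm. Relationship dissolution is itself one of the safety outcomes compared between arms, so equality cannot be presumed.

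**Working it through.** The article gives no rate, IRR or event count for this outcome, so there is no stated figure to reproduce.

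**Inputs from the article:** recall window 3 months (Outcomes); four follow-up visits over 24 months (Design); 165 couples (Sample Size); 13 of 160 couples separated so far, split by arm not given (Results); follow-up after separation (Couple Dissolution).

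**Assumptions, for illustration only:** true rates of 40 (control) and 30 (intervention) acts per couple-year; complete follow-up; recalled months representative of the unrecalled ones; separations at 12 months, with the HIV-negative partner's one further visit at 18 months.

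**Step 1: coverage.** 4 × 3 = 12 of 24 months, or 0.5. For 165 couples, follow-up is 165 × 2 = 330 couple-years or 660 person-years, of which recall covers 330 × 0.5 = 165 couple-years.

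**Step 2: reported rate relative to the true rate per couple-year.** Factor = (reports counted per act) × (recalled months ÷ months in the denominator) ÷ (persons' time counted per couple).

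| Act counted | Denominator | All follow-up time | Recalled time only |
|---|---|---|---|
| Once per couple | Couple-years | 0.5 | 1.0 |
| Once per couple | Person-years, both men | 0.25 | 0.5 |
| Both reports summed | Couple-years | 1.0 | 2.0 |
| Both reports summed | Person-years, both men | 0.5 | 1.0 |

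With all follow-up time in the denominator, the understatement is 1-fold to 4-fold. The value 1.0 in that column arises only because double counting offsets the lost recall time. The last column shows that matching the time alone is not enough: without a counting rule the factor still runs from 0.5 to 2.0.

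**Step 3: example.** At 40 acts per couple-year, four windows capture 40 × 0.25 × 4 = 40 acts. Over 2 couple-years that is 20 per couple-year; over 4 person-years it is 10 per person-year.

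**Step 4: rate ratio with a common factor.** 30/40 = 15/20 = 7.5/10 = 0.75. The factor cancels.

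**Step 5: rate ratio with unequal dissolution.** An intact couple gives 4 person-years and λ recalled acts (λ × 2 × 0.5), where λ is the true rate per couple-year. A couple separating at 12 months gives 2 + 1.5 = 3.5 person-years and 0.5λ acts. With 5% (control) and 11% (intervention) separating:

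- Control: 40 × (0.95 + 0.025) = 39.0 acts over 0.95 × 4 + 0.05 × 3.5 = 3.975 person-years, giving 9.81.
- Intervention: 30 × (0.89 + 0.055) = 28.35 acts over 0.89 × 4 + 0.11 × 3.5 = 3.945 person-years, giving 7.19.
- IRR: 7.19/9.81 = 0.73, against a true 0.75.

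The same calculation gives 0.75 for 8% v 8%, 0.70 for 0% v 16%, and 0.80 for 16% v 0% (control v intervention). With couple-years that stop at separation, the 5% v 11% case gives (28.35/1.89) ÷ (39.0/1.95) = 15/20 = 0.75, and the ratio stays at 0.75 in the other cases too.

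**The case against.** The best defence has four parts.

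1. **The 6-monthly counts may simply be counts taken at each 6-monthly visit**, with the offset and the reconciliation of the partners' reports left to an analysis plan that is not shown. The article does not exclude rescaling, so the twofold figure is conditional on none being applied. But the section fixes the numerator, denominator, model, software procedure and correlation structure, and the denominator it names is follow-up time. That is a stated rule that does not fit the data collected, not an omitted detail.
2. **A reader might infer that every reported rate must be wrong by a factor of 2 to 4.** The documents do not support that. The factor depends on an unstated counting rule and can be 1. Part of the 4 is only a change of unit: 10 per person-year and 20 per couple-year are the same rate, and the 4 appears only if the person-year figure is read as a couple-year rate.
3. **A reader might infer that the treatment comparison is wrong by the same factor, or that missed visits bias it.** A common factor cancels from the IRR. Nothing says that a missed visit adds event-free time, and in a GEE on repeated counts an interval without a count ordinarily contributes no record. The Results report average retention of 95% and more than 90% at 24 months, with no arm difference shown.
4. **Couple-years, and couples as the repeated unit, already suggest that time stops at separation.** That is a fair reading of those sentences, but it contradicts the person-year sentence, and the text does not say which governs.

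**Conclusion.** The point holds for the absolute rates. The stated denominator does not match the 3-month recall, and one rate is given two units. Without rescaling, and with each act counted once per couple-year, incidence density is understated by a factor of 2. Across the counting rules that the text leaves open, the understatement relative to the true couple-year rate is 1-fold to 4-fold.

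The between-arm IRR is largely protected. It shifts only on the person-year reading and only if dissolution differs by arm: from 0.75 to about 0.73 in the 5% v 11% example, and to 0.70 or 0.80 in the extreme splits tried. The arm-specific rates and break-up percentages are assumptions; only the overall 13/160 is reported. The cancellation also assumes that the recalled half of each interval represents the other half equally well in both arms.

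This should be fixed, but it is not critical. It concerns a secondary outcome; engagement in care and viral suppression are untouched.

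**What to change.** Reword the section so that the rate has one unit and matched time:

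- Make the couple the single unit. Count each act once, from one partner's report named in advance, and use the other partner's report as a sensitivity analysis.
- Model the 3-month count at each completed interview in PROC GENMOD, with offset log(0.25 year).
- Shorten the offset where the original couple was together for only part of the window. Drop the record where they were not together at all, and accrue no time after dissolution.
- Report rates per couple-year of recalled time, delete the person-year wording, and describe the counts as 3-month counts at 6-monthly visits. Use the same denominator for the exact Poisson analysis of sparse subgroups.

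A couple-level permutation test in place of exact Poisson would respect the clustering of acts within couples, but that is a separate, optional refinement.

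The cost is a few sentences and one derived offset variable. No new data are needed; the bi-monthly calls, which already ask about the relationship, may help to date separations. The offset does not recover the unrecalled months, so the report should say that the rate refers to the 3 months before each visit.

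### Below 15 events the plan compares at-risk sex acts by exact Poisson methods, which ignore repeated acts by one couple, so p-values and IRR intervals in sparse subgroups can be too optimistic

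*Protocol article*

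**What the plan says.** All of this is in the protocol article, section on the incidence of aggregate sex at risk within partnerships.

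- **Event.** "At-risk sex will be defined as any CAI that occurs within the partnership during the follow-up period". The rate is formed "with the numerator being number of individual at-risk sex acts, and the denominator being person-years of follow time". It is a recurrent event, not a first event or a yes/no status per couple.
- **Sparse branch.** Rates are compared "using exact methods based on the Poisson distribution when there are fewer than 15 events per subgroup".
- **Other branch.** The comparison is made "when there are at least 15 events per group, by using the GEE approach".
- **Allowance for couples.** The GEE Poisson regression of 6-monthly counts is fitted "using an exchangeable correlation structure for the repeated observations of couples". No couple-level or overdispersion term is attached to the exact methods.
- **Reporting.** An IRR with a 95% confidence interval is promised by each baseline covariate (race, age, duration of relationship).

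The Design section sets the exposure: "Couples are followed prospectively for 24 months, with study assessments at baseline, 6, 12, 18, and 24 months". Under Outcomes, each man estimates how many anal sex acts he had with his main partner and how many of them were condom-protected. The data therefore arrive as a count per couple and visit.

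**The concern.** An exact Poisson comparison is exact only if acts occur independently at a constant rate. Acts within one partnership do not: some couples have none and others have several. The plan accepts this in its GEE regression and drops it below 15 events, where one or two couples can make up most of the count. This is not detail left to an analysis plan, because the article names both the method and its trigger.

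At stake is a false finding in a small subgroup. A difference produced by two or three couples could carry a small p-value and an IRR interval that excludes 1, with the word exact lending it authority.

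**Working it through.** The plan gives no event rate or error rate for this comparison, so there is no figure to reproduce.

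**1. What clustering does to the variance.** Let each of n couples report any act with probability p, and let a reporting couple's acts be geometric with mean m and variance m(m − 1).
- Mean per arm = npm.
- Variance per arm = np·m(m − 1) + np(1 − p)·m².
- Variance/mean = (m − 1) + (1 − p)m = 2m − 1 − pm.

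For small p this is about 1, 3, 5 and 9 at m = 1, 2, 3 and 5. The exact Poisson test takes it as 1.

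**2. A worked case.** Take equal person-time and 3 versus 12 acts, each arm below 15.
- Conditional exact test: p = 2 × (1 + 15 + 105 + 455)/2^15 = 1152/32768 = 0.035.
- IRR = 3/12 = 0.25, Clopper-Pearson 95% interval 0.05 to 0.93.

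Suppose the 3 acts come from one couple and the 12 from two couples (7 and 5). Moving whole couples between arms gives four splits of about equal probability: 15|0, 12|3, 10|5 and 8|7. Two of the four differ by at least 9, so p = 0.50. If the acts come from six couples (2, 1 against 4, 3, 3, 2), the permutation p is 0.25. The exact Poisson p is 0.035 in both cases, because it uses only the totals.

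If the threshold of 15 is read as the total over both arms, 2 versus 12 acts (total 14) makes the same point: p = 2 × (1 + 14 + 91)/2^14 = 212/16384 = 0.013.

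**3. Type I error when the branch applies.** Simulation with no arm effect and equal follow-up, using the model of step 1. The test is the two-sided doubled-tail exact test at 5%, applied when both arms have fewer than 15 acts. *From the document:* 165 couples and 80% retention, so 165 × 0.80 = 132 couples, or 66 per arm if split equally. *Assumed:* the subgroup sizes, the share of couples reporting any act, and the mean acts per reporting couple.

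| Couples per arm | Share reporting | Mean acts per reporting couple | Actual error |
|---|---|---|---|
| 10 to 22 | 10 to 20% | 2 to 5 | about 8 to 27% |
| 10 | 20% | 1.5 | about 5% |
| 10 | 20% | 2; 3 | about 12%; 20% |
| 66 | 3 to 5% | 2 to 5 | about 13 to 28% |
| 66 | 10% | 2 to 5 | about 5 to 9% |
| 66 | 20% | 2 to 5 | at or below 5% |

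With one act per reporting couple the test is conservative: 0.3 to 1.8% with 66 per arm and 5 to 12 expected acts per arm.

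**4. How often the branch would be used.** In whole arms, 66 couples × 10% × 1 act a year × 2 years = 13.2 acts; at 30% reporting it is 39.6. With 10% reporting, both arms fall below 15 acts in 39%, 10% and 1.5% of trials at means of 2, 3 and 5. The rule therefore matters mainly in subgroups.

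**The case against.** The strongest case against the point concerns its reach and size. A reader might infer that the type I error is several times nominal whenever this rule is used, or that the overall arm comparison is unsafe. The document supports neither.

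- **Overall comparison.** Any condomless act counts, even under PrEP or viral suppression, over 24 months in committed couples, so arm totals would probably pass 15. The regression of 6-monthly counts is stated without an event threshold and models couple correlation.
- **Size.** The exact test is conservative at low counts and can absorb mild clustering. Large inflation in whole arms needs about 5% or fewer of couples to report any act. That share matters as much as the acts per couple, and the document gives neither.
- **Importance.** Sexual risk-taking is secondary. The primary outcomes are engagement in care and viral suppression, and they are not touched.

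All three stand as limits. They do not remove the point: the rule is written for subgroups, covariate-specific IRRs with intervals are promised, and inflation persists with 10 to 22 couples per arm. A fair objection also applies to the remedy. Replacing the comparison by Fisher's test on any act would change the quantity from a rate to a proportion and would give no IRR.

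**Conclusion.** The point holds in a conditional form. The sparse-branch rule does not fit its own event unit, and p-values and IRR intervals in sparse subgroups of this secondary outcome can be too optimistic.

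The mechanism is certain; the size is not. The figure of about 8 to 27% against a nominal 5% rests on assumed subgroup sizes, reporting shares and geometric acts per couple, and on reading the threshold as applying to each arm. Under other plausible values the test is near or below nominal. The change is worth making because it is cheap and the wording is already fixed in the plan.

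**What to change.** Replace the exact Poisson branch with a method that keeps the couple as the unit:

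- **Test.** A permutation test of the rate ratio (or rate difference) that permutes arm labels across couples, each couple carrying its acts and follow-up time together. This mirrors the Randomization section, where couples are allocated singly by one generator.
- **Estimate.** Report the IRR with an interval that allows for couple clustering. When too few couples contribute any act, report it descriptively, with the number of contributing couples beside the number of acts. State in advance how few is too few.
- **Supporting analysis, optional.** Fisher's exact test on the proportion of couples with any at-risk act, labelled as a different estimand.

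The cost is a sentence or two of wording and a few lines of code, with no change to data collection. The price is less precise, or only descriptive, IRRs in sparse subgroups.
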